## Abstract

**Background:**

Postoperative nausea and vomiting (PONV) are common in posterior lumbar intervertebral fusion (PLIF) patients undergoing general anesthesia. The previous clinical observation has shown that a traditional acupoint herbal plaster (AHP) is beneficial to patients with PONV. This trial aims to assess the effect of the AHP for the prevention and treatment of PONV after PLIF in patients with general anesthesia.

**Methods:**

A multicenter, parallel, randomized controlled trial (RCT) will be conducted. A total of 166 participants will be randomized to either a treatment group receiving an AHP or a control groups receiving an acupoint placebo plaster (APP) in a 1:1 ratio. The primary outcomes are the first occurrence and frequency of nausea and vomiting. The secondary outcomes include the severity grading of nausea and vomiting using a visual analog scale (VAS) measurement system, quality of life, and serological indicators. The safety evaluation is mainly about adverse events and skin reactions’ observation. Assessments will be carried out at the baseline, day 1, and day 2 (the end of the intervention). The central randomization system in the clinical trial (http://124.205.181.142:8082/xwtf/) will be used to conduct random allocation.

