### Objectives {7}

The hypotheses are as follows.

Confirmatory test for AHP versus APP:
H0: Effect of AHP ≤ Effect of APPH1: Effect of AHP > Effect of APP

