### Outcomes {12}

#### Primary outcome

##### The first occurrence and frequency of PONV

The primary outcome will be recorded within the postoperative 48 h. The important index will be self-reported daily and recorded in a diary during the treatment course. In the meantime, each participant will be face-to-face interviewed to attend an in-person assessment at the orthopedic inpatient department.

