### Sample size {14}

A relatively small number of clinical trials has investigated the effects of acupoint plaster on PONV; however, the research results are not appropriate to calculate the sample size for this study. The sample size is calculated based on the primary endpoint. The small sample-size clinical practice suggests the decreased rate of nausea and vomiting frequency is 60% in the treatment group, while the rate is 40% in the control group based on previous literature. According to the superiority test, it is estimated that at least 69 participants per group are needed when the study achieves 90% power and a two-sided 5% significance level. Given the dropout rate to 20%, the sample size in the clinical trial sets at a total of 166 cases, and each group is 83 cases.

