### Statistical methods

#### Statistical methods for primary and secondary outcomes {20a}

The efficacy and safety analysis will be conducted according to the intention-to-treat principle. As the third party, the statistical analysis will be performed by the Institute of Clinical Basic Medicine, China Academy of Chinese Medical Sciences, using the statistical packages of social sciences software (SPSS; version 19.0). All the results are based on two-sided tests. Continuous data will be presented as means and standard deviations and compared using the independent *t* test or Wilcoxon’s rank-sum test. On the other hand, categorical data will be presented as percentages and frequencies and analyzed using the chi-square or Fisher’s exact test. The missing values will be implemented by the method of multiple imputations. A *p* value less than or equal to 0.05 will be considered statistically significant.

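### At least two primary variables share one confirmatory claim at an unadjusted 0.05, and the protocol does not say which of them decides it

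*Protocol article*

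**What the plan says.** The protocol article touches on the primary comparison in five places.

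- **Abstract, Methods:** the primary is plural. "The primary outcomes are the first occurrence and frequency of nausea and vomiting".
- **Outcomes {12}, Primary outcome:** the heading is singular, but the item beneath it still joins two variables, "The first occurrence and frequency of PONV", with PONV treated as one entity. The window is given: "The primary outcome will be recorded within the postoperative 48 h".
- **Objectives {7}:** one directional hypothesis, introduced as "Confirmatory test for AHP versus APP". It concerns the effect of each plaster, and no variable is attached to it.
- **Sample size {14}:** "The sample size is calculated based on the primary endpoint", in the singular. The inputs describe frequency only: "decreased rate of nausea and vomiting frequency is 60% in the treatment group, while the rate is 40% in the control group". The full two-sided 5% is spent on this one comparison, with 90% power.
- **Statistical methods {20a}:** "All the results are based on two-sided tests", and a p "value less than or equal to 0.05 will be considered statistically significant". This rule covers all results alike.

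None of these sections gives a hierarchy, a split of alpha, a rule that all must succeed, or a rule that any one suffices.

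**The concern.** A confirmatory trial's 5% level and its power both belong to a decision rule. Here there is one hypothesis and one sized endpoint, but at least two variables carry the label primary, and nothing connects them. The rule could therefore be settled after the results are seen, and efficacy could be claimed from whichever variable came out well. Depending on the rule eventually adopted, either the 5% significance level or the power quoted in Sample size {14} would not be a property of the design.

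**Working it through.** **Inputs.** Two-sided α = 0.05 per test (Statistical methods {20a}). Number of primary tests k = 2 if PONV is one composite (Outcomes {12}), or k = 4 if the abstract is read as separating nausea from vomiting. The correlation r between test statistics is not given, so it is shown as a range.

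**The plan's own figure.** For 60% vs 40%, 90% power and two-sided 5%, the pooled two-proportion formula gives

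n = [1.96·√(2·0.5·0.5) + 1.2816·√(0.6·0.4 + 0.4·0.6)]² / 0.2² = (1.386 + 0.888)² / 0.04 ≈ 129.3, so 130 per group.

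The protocol states 69. That figure is not reproduced: 69 per group gives about 65% power. The step from 69 to 83 is 69 × 1.2 = 82.8. The shortfall is a separate matter. It bears on this point only in that 90% is the stated power, not the power that follows from the inputs.

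**Rule A: either variable suffices.** With independent tests the family-wise error is 1 − (1 − α)^k.

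- k = 2: 1 − 0.95² = 9.75%
- k = 4: 1 − 0.95⁴ = 18.5%

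Objectives {7} is directional, so the harmful error is a false claim for the herbal plaster, nominally 2.5% per two-sided test.

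- k = 2: 1 − 0.975² = 4.9%
- k = 4: 1 − 0.975⁴ = 9.6%

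For correlated tests, equicorrelated normal statistics were simulated (1,000,000 draws per setting):

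| r | k = 2, two-sided | k = 2, favouring AHP | k = 4, two-sided | k = 4, favouring AHP |
|---|---|---|---|---|
| 0 | 9.7% | 4.9% | 18.5% | 9.6% |
| 0.5 | 9.1% | 4.5% | 15.6% | 7.8% |
| 0.7 | 8.4% | 4.2% | 13.1% | 6.5% |
| 0.8 | 7.8% | 3.9% | 11.4% | 5.7% |
| 0.9 | 7.1% | 3.5% | 9.3% | 4.7% |

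**Rule B: both must succeed.** The chance of a false claim is at most 5%. Power falls instead. If the second variable also had the stated 90% power (an assumption, as none is given for it), joint power would lie between 0.9 × 0.9 = 81% (independent) and 90% (perfectly correlated). Starting from the 65% that 69 per group gives, the range is 0.65 × 0.65 ≈ 42% to 65%.

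**Rule C: one designated variable.** The error is 5% and the sizing applies to that variable. Sample size {14} points this way, but no section makes the designation.

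**The case against.** The strongest reply is that the trial may really have one primary endpoint. The Outcomes heading is singular, Sample size {14} speaks of a single primary endpoint, and its rates concern frequency. An analysis plan that is not shown could hold the decision rule, and a journal article need not repeat it. This has force as to intent, and it shows which variable to designate. It does not remove the conflict, because the article itself gives primary status to two variables and sets one unadjusted threshold for all results.

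A second reply concerns size. First occurrence and frequency come from the same events: a patient without PONV has no first occurrence and a frequency of zero. The two tests are probably strongly correlated, so 9.75% is a ceiling and about 7–9% more realistic. Counting only claims in favour of the herbal plaster, two tests stay below 5%. Both observations stand, although the latter is still inflation over the nominal 2.5%.

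A reader might infer that success on any one variable rejects the null, so that the error rate is simply well above 5%. The documents do not say this. They are silent on the rule, and if both variables must succeed there is no inflation. A reader might also count four tests. That needs the abstract's phrase to be split in a way that neither Outcomes {12} nor Sample size {14} does, so the 18.5% belongs to a less likely reading.

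**Conclusion.** The point holds as a conflict within the protocol: two primary variables, one hypothesis on an undefined effect, one sized endpoint, one unadjusted threshold and no decision rule. Its consequence is conditional.

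- If either variable suffices, the two-sided family-wise error is up to 9.75%, and about 7–8% at correlations of 0.8–0.9. False claims for the herbal plaster rise from 2.5% to at most about 4.9%, taking the correlation as non-negative.
- If nausea and vomiting are also tested separately, the two-sided figure is up to 18.5%.
- If both must succeed, the error is at most 5%, but the single-endpoint power no longer describes the trial.

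The correlation and the number of tests are assumptions, because the protocol gives neither. An unconditional statement that the trial's error rate exceeds 5% is not supported. What is supported is that the 5% level and the stated power cannot both be relied on until the rule is fixed.

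**What to change.** Before unblinding, designate one primary variable and define it explicitly (what counts as an event, the 48-hour window, and how each patient is summarised). The natural choice is the frequency-based endpoint on which Sample size {14} rests. Attach the hypothesis in Objectives {7} to it. Then test the other variable in fixed sequence at two-sided 5%. If the sponsor prefers to keep both as primary, use Holm. Report nausea and vomiting separately as descriptive components.

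If the proportion with any PONV over 0–48 h is chosen instead, the sample-size inputs must be restated. The 60% vs 40% is a reduction rate, where higher is better. Read as incidence, it would have the herbal plaster doing worse than placebo.

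**Cost.** The fixed sequence keeps the full 5% for the first test and needs no extra patients for multiplicity, but the second variable can be claimed only if the first succeeds. Under Holm the smaller p-value must first pass 0.025. On the plan's 60% vs 40%, power for a single test at that level with 69 per group is 54%, against 65% at 0.05, and 90% power would need 153 per group rather than 130. The text change is short, but recruitment began in May 2018 (Trial status), so it amends a running trial. It has to be notified in writing as the section on protocol amendments {25} requires, and the registry entry updated.

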**Discussion:**

This scientific methodology design of the trial is expected to provide clinical evidence to support the AHP for the prevention and treatment of PONV.

**Trial registration:**

This study is retrospectively registered with the Chinese Clinical Trial Registry (http://www.chictr.org.cn) on 19 April 2018. ID: ChiCTR1800015768.

## Administrative information

The order of the items has been modified to group similar items (see http://www.equator-network.org/reporting-guidelines/spirit-2013-statement-defining-standard-protocol-items-for-clinical-trials/).

## Introduction

### Background and rationale {6a}

Postoperative nausea and vomiting (PONV) are some of the most common and undesirable side effects of conventional anesthesia surgery [1–3]. The incidence of PONV after general anesthesia may reach as high as 30~50% [4]. PONV could also lead to serious complications, such as hematoma, surgical incision hemorrhage, pulmonary aspiration, wound dehiscence, and dehydration, aspiration pneumonia, and increased intracranial pressure [5–8]. On the other hand, PONV was likely to reduce patients’ satisfaction, delay discharge and recovery, and increase medical costs [9, 10]. Therefore, unignorable complication still poses a severe challenge for anesthesiologists, clinicians, and researchers.

Existing consensus guidelines from the American Society for enhanced recovery (ASER) recommended a variety of medications that worked at different receptor sites, such as antihistamines, steroids, and so on [11]. However, no single antiemetic drug could fully respond to prophylaxis and management of PONV, and high-risk individuals often did not receive appropriate antiemetic prophylaxis [12]. Besides, traditional drug therapy had its obvious side effects, while the costs of new agents including NK1-antagonists or the newer 5-HT3 antagonists became relatively higher [13, 14]. On the contrary, more and more turned to alternative and complementary medicine, including herbal medications, acupressure, and so on [15–17].

Non-pharmacologic therapies are also a considerable therapeutic method for PONV [11]. Among the therapeutic methods, traditional Chinese medicine (TCM) therapy regimen including acupuncture, acupressure, and acupoint herbal plaster (AHP) was commonly used based on the treatment principle of “descending stomach qi”. Because the postoperative patients could not immediately eat more within 6 to 8 h, so oral Chinese medicine is not often taken in the treatment of PONV. AHP, by contrast, became a relatively appropriate choice and was easier for patients to accept. As one type of TCM method, herbal plaster was applied with a drug applicator using the mature technique, stimulating the skin at specific acupoints [18]. Our team previously completed the 36 cases clinical observation of AHP for the prevention and treatment of PONV after surgery [19]. It was found that AHP at Neiguan (PC6) and Zhongwan (CV12) had a definite effect in relieving the symptoms of PONV. The Chinese herbal formula which is used in the plaster consist of three commonly used herbs: ginger pinellia (Jiangbanxia, Pinelliae Rhizoma Praeparatumcum Zingibere Et Alumine), ginger (Shengjiang, Zingiberis Rhizoma Recens), and *Syzygium aromaticum* (Dingxiang, Caryophylli Flos). And the formula contained *Xiao Banxia decoction* (ginger pinellia and ginger) which was documented in *Shang Han Za Bing Lun*, a classic medical book dating as far back as the Han Dynasty [20]. It could be considering treating all kinds of vomiting. Additionally, PC6 and CV12 had been also the primary choice for the treatment of nausea and vomiting and closely related to gastrointestinal function [21–23].

Having given this, we make the further design and conduct the randomized controlled trial (RCT) to assess the efficacy and safety of AHP for PONV. As far as we know, this study is the first RCT to verify the effect of AHP for the prevention and treatment of PONV.

### Objectives {7}

The hypotheses are as follows.

Confirmatory test for AHP versus APP:
H0: Effect of AHP ≤ Effect of APPH1: Effect of AHP > Effect of APP

### Trial design {8}

This study is a multicenter, prospective, and double-blind RCT. Ethical approval has been obtained from the ethical committee of Wangjing Hospital, China Academy of Chinese Medical Sciences (No. WJEC-KT-2018-001-P002). This study is registered on chictr.org.cn (ChiCTR1800015768). A brief flow diagram of the entire study is shown in Fig. 1.

**Fig. 1 Fig1:**
[figure not shown]
Flow diagram of enrollment, interventions, and assessments

The screening and enrollment will be done before the day of treatment on day zero. All the treatments will be scheduled from day 0 to day 2. The study protocol procedure includes the recommended elements in the Standard Protocol Items: Recommendations for Interventional Trials (SPIRIT) checklist [24]. The schedule of events is provided in Fig. 2.

**Fig. 2 Fig2:**
[figure not shown]
SPIRIT Checklist. T1, pre-operation; T2, postoperative 8 h; T3, postoperative 24 h; T4, postoperative 48 h

## Methods: participants, interventions, and outcomes

### Study setting {9}

The patients will be recruited from the orthopedic inpatient department from the three affiliated hospitals of China Academy of Chinese Medical Sciences, including Wangjing Hospital, Xiyuan Hospital, and Guanganmen Hospital.

### Eligibility criteria {10}

The participants who meet the following criteria are eligible: (1) PLIF with general anesthesia, (2) aged from 30 to 65 years old, (3) body mass index ranged from 20 to 25 kg/m^2^, and (4) anesthesia grade scale of the American society of anesthesiologists (ASA) judged as I or II Level.

### Who will take informed consent? {26a}

Informed consent will be obtained from all participants before entry into the trial including the possible risks, benefits, and knowledge of the purpose of the trial.

### Additional consent provisions for collection and use of participant data and biological specimens {26b}

This study involves a questionnaire survey and blood sample collection, which is carried out at the same time by medical examination before and 24 h after surgery. Five milliliters of serum will be collected twice, and the remaining blood samples will be treated as abandoned blood after the test. The blood samples of the subjects will be indicated by the study number instead of the name. Unless the consent of the subjects is obtained, the information that can identify the subjects will not be disclosed to members outside the study group.

All members of the study and the sponsor are required to keep the identity of the subjects confidential, and the files will be kept in a locked file cabinet for the researchers’ reference only. To ensure that the research is carried out under the regulations, if necessary, the management department of the research institute or members of the ethics committee may consult the personal data of the subjects in the research unit. When the results of the study were published, no information about the subjects was disclosed.

### Interventions

#### An explanation for the choice of comparators {6b}

All the participants who provide informed consent will be randomized into either a treatment group receiving a 2-day AHP or a control group receiving a 2-day APP. A block randomization sequence using a web-based allocation system will be generated by a central randomization system. The system is managed by the Institute of Clinical Basic Medicine, China Academy of Chinese Medical Sciences. Three practitioners from the different units will apply for the random number from the randomization system, and treatment allocation is determined based on the web the day before the operation.

All the plasters used in the RCT have a similar appearance, smell, and size to ensure the practitioners and patients impossible to distinguish the treatment allocation. Furthermore, the plasters will be packed and labeled to ensure that the researchers and the subjects involved in the study will remain fully blinded as to the identity of the treatment administered. Outcome assessors, laboratory technicians, data managers, and statisticians will not know the treatment allocations, which will be revealed at the end of the trial.

#### Intervention description {11a}

According to the domestic and international expert opinion, all the enrolled patients are given 4-mg Torasetron hydrochloride intravenously at the end of operation [4, 11]. All treatment details will be standardized between practitioners by guiding videos and relevant training before the first treatment session. The acupoint location is based on Term and Location of Acupoints (GB/T12346-2006) issued by the State administration of standardization. The plasters will be attached on the acupoints of bilateral PC6 and RN12 for at most 6 h each time.

##### Experimental group

The patients in the experimental group will receive a 2-day AHP plus conventional Torasetron hydrochloride therapy. Treatment procedures in sequential order are to locate the acupoints, disinfect the skin, and attach the plaster on the skin over the acupoints. It must be removed immediately if an allergic reaction occurs, which may be described by patients as a burning sensation, severe itchiness, blisters, pruritus, or rash on the local skin. A total of 2 sessions will be performed 24 h and 48 h after the operation. The treatment starts before anesthesia before the operation, with at most 6 h of treatment twice per day.

##### Control group

The patients in the control group will receive a 2-day APP plus conventional Torasetron hydrochloride therapy. The treatment procedures between the groups are identical; the only variable is the ingredients of paste.

### Preparation of the plasters

In this study, there are two types of paste to be applied on the sticky plasters: herbal paste for the AHP group, and buckwheat paste for the APP group (Fig. 3c and d). In the previous clinical observations, we adapted this formula and standardized its performance. AHP and APP in the trial will be manufactured by the School of Chinese Materia Medica of Beijing University of Chinese Medicine based on the good manufacturing practice (GMP) standards.

**Fig. 3 Fig3:**
[figure not shown]
Illustration of the sticky plaster. **a**, **b** The anterior and posterior appearance of the acupoint plaster, respectively. **c**, **d** The paste inside the plaster. **c** The herbal plaster. **d** The buckwheat plaster. These two kinds of paste are identical in appearance and smell. Figures are only for illustrative purposes

In the AHP group, the standard operating procedures are listed as follows.
Prepare the herbal materials: the formula includes ginger pinellia, ginger, and *Syzygium aromaticum*. The ingredients of this formula are mixed in a weight ratio of 1:1:1 and then the raw materials ground into a fine powder (200 mesh screen) using a special Chinese medicinal crop powder mixer.Add the liquid base: a total of 100-g mixed herbal powder is put into a container. Fifty-gram honey is added and stirred well to make a thick herbal paste.Make the sticky plaster: a round powder cake of the herbal paste is placed on the medical desensitization sticky plaster. The sticky plasters are sized 6 × 6 cm^2^ with a diameter of 2 cm and a thickness of 0.2 cm in the middle of which is placed the host herbal paste (Fig. 3a and b). The rest of the sticky plaster carries no herbal paste, which makes it adhere to the skin over the acupoints.

For the APP group, the placebo paste is made of buckwheat flour with 5% herbal medicines original concentration. It is still mixed with honey to maintain a similar appearance and smell with the AHP. So, the plasters used in two groups are undistinguished to the patients and practitioners.

### Criteria for discontinuing or modifying allocated interventions {11b}

The trial can be stopped in case of other diseases or aggravation during the trial.The trial can be stopped in case of emergency or serious adverse events.If the patient withdraws from the trial or fails to continue the trial, or fails to cooperate with the treatment, the trial can be stopped.During the period of patients participating in the trial, the occurrence of infection affects the data of this trial, and the trial can be stopped.

